## Abstract

**Background:**

Depression and bipolar disorder are associated with reduced neural plasticity and deficits in memory, attention and executive function. Drug treatments for these affective disorders have insufficient clinical effects in a large group and fail to reverse cognitive deficits. There is thus a need for more effective treatments which aid cognitive function. Erythropoietin (Epo) is involved in neuroplasticity and is a candidate for future treatment of affective disorders. The investigators have demonstrated that a single dose of Epo improves cognitive function and reduces neurocognitive processing of negative emotional information in healthy and depressed individuals similar to effects seen with conventional antidepressants. The current study adds to the previous findings by investigating whether repeated Epo administration has antidepressant effects in patients with treatment resistant depression and reverses cognitive impairments in these patients and in patients with bipolar disorder in remission.

**Methods/design:**

The trial has a double-blind, placebo-controlled, parallel-group design. 40 patients with treatment-resistant major depression and 40 patients with bipolar disorder in remission are recruited and randomised to receive weekly infusions of Epo (Eprex; 40,000 IU) or saline (NaCl 0.9%) for 8 weeks. Randomisation is stratified for age and gender. The primary outcome parameters for the two studies are: depression severity measured with the Hamilton Depression Rating Scale 17 items (HDRS-17) [1] in study 1 and, in study 2, verbal memory measured with the Rey Auditory Verbal Learning Test (RAVLT) [2,3]. With inclusion of 40 patients in each study we obtain 86% power to detect clinically relevant differences between intervention and placebo groups on these primary outcomes.

**Trial registration:**

The trial is approved by the Local Ethics Committee: H-C-2008-092, Danish Medicines Agency: 2612-4020, EudraCT: 2008-04857-14, Danish Data Agency: 2008-41-2711 and ClinicalTrials.gov: NCT 00916552.

## Background and objective

### Background

Depression and bipolar disorder are associated with neurodegenerative processes, reduced neuroplasticity and neuropsychological dysfunction, which often persist even after clinical remission. Current pharmacological treatment strategies have several limitations including a significant treatment-onset-response delay, only partial or no response in a large group of patients and limited effects on their cognitive deficits, which often persist into periods of remission [4-9]. These enduring cognitive impairments affect patients' psychosocial and occupational function, quality of life and prognosis [7,8,10,11]. Better treatment options are thus required to improve the onset of efficacy, address patients who are treatment resistant and remediate neurocognitive deficits. Converging evidence suggests that neural atrophy and reduced neuroplasticity are involved in depression and bipolar disorder, while restoration of synaptic plasticity may be an important mechanism of chronic antidepressant and mood stabilising drug treatment [12-14]. This hypothesis is supported by evidence that increased hippocampal brain-derived neurotrophic factor (BDNF) is necessary for the behavioural effects of antidepressant treatment [15] and that infusion of BDNF into the hippocampus mimics the behavioural effects of antidepressants in rodents [16]. These effects and the role of BDNF in learning and memory suggest that compounds, which induce rapid and prolonged upregulation of neuroplasticity, may reduce the latency to antidepressant effects and alleviate neurocognitive dysfunction.

Erythropoietin (Epo) has interesting properties, which make it a candidate for investigation as a novel therapeutic agent in neuropsychiatric diseases. It is used for the treatment of anaemia but has received renewed attention because of its direct neurobiological actions mediated through a non-haematopoietic Epo receptor system in the brain [17]. Systemically administered Epo crosses the blood-brain barrier (BBB) and has neuroprotective and neurotrophic effects in animal models of acute brain damage and chronic neurodegenerative conditions [18,19]. In humans, repeated Epo administration improves neuropsychological function in patients with schizophrenia [20] and multiple sclerosis [21]. Several complex biochemical pathways mediate these actions, including rapid up-regulation of neuroplasticity mechanisms including BDNF and neurogenesis [22,23], and anti-inflammatory actions [24,25].

Functional magnetic resonance imaging (fMRI) evidence highlights the functional neuroanatomy of emotional processing and working memory as potential neurobiological markers for depression [26,27]. Antidepressant drugs with different neurochemical actions show similar effects in such human biomarker models relevant to depression and antidepressant effects. In particular, serotonergic and noradrenergic antidepressants increase the neural and cognitive processing of positive emotional information and down-regulate the processing of negative threat-relevant information after acute and 7 days administration and in the absence of changes in mood in healthy volunteers [28,29] and in depressed patients [30]. Such actions contrast with heightened recognition and neural responses to threatening information in depression [31,32] and may be an important mechanism of antidepressant drug treatment. We have recently reported cognitive and neural effects of a single dose of Epo (40,000 IU; i.v.) in human models of antidepressant drug action independent of any haematological effects in healthy volunteers [33-36]. In particular, Epo enhanced memory-relevant hippocampal engagement during picture retrieval 1 week post administration [34] consistent with increased hippocampal BDNF and plasticity [37,38]. Epo also modulated fronto-parietal activation during spatial working memory (WM) and improved verbal fluency performance at this time after administration [35]. Finally, Epo reduced parietal-occipital activation during presentation of fearful facial expressions and the behavioural recognition of this emotion [33] consistent with decreased attentional processing and perception of threat-relevant stimuli 7 days post administration similar to effects seen with conventional antidepressant drug administration to healthy volunteers [28,29]. Notably, we demonstrated a similar reduction in the neural and cognitive response to negative threat-relevant picture stimuli following a single dose of Epo vs. placebo to acutely depressed patients [39]. Together with its known effects on neuroplasticity in animal models, these findings highlight Epo as a new candidate treatment for affective disorders.

### Objective

The aim of the study is to investigate whether these early effects of Epo translate into improvement of mood and neurocognitive function with repeated administration in patients with treatment-resistant depression or bipolar disorder in remission and to elucidate the underlying biomarkers of potential treatment effects. Beneficial effects on these measures would highlight Epo as a candidate for adjunct treatment for affective disorders to attenuate mood symptoms and aid cognitive function in these patients groups.

## Methods

### Study design

The present trial has a double-blind, placebo-controlled, parallel-group design in which participants are randomised to receive weekly infusions of either Epo (Eprex; 40,000 IU; Janssen-Cilag) or saline over 8 weeks. Patients complete a broad neurocognitive test battery assessing memory, executive function and attention at baseline, after completion of treatment (week 9) and at follow-up (week 14). Mood, symptoms and quality of life are measured at baseline and weeks 5, 9 and 14 using a variety of rating scales including the Hamilton Depression Rating Scale 17 items (HDRS-17) [1], Young Mania Rating Scale (YMRS) [40], Beck Depression Inventory (BDI) [41], Massachusetts General Hospital Cognitive and Physical Functioning Questionnaire (CPFQ) [42], and the EuroQol visual analogue scale (VAS) for quality of life (EQ-5D) [43]. Patients undergo an fMRI scan at baseline and week 14. Further, plasma and whole blood BDNF and inflammatory markers will be investigated with blood tests at baseline and weeks 5, 9 and 14. Finally, we will assess metabolic parameters with blood tests at baseline and weeks 5, 9 and 14, and body fat mass by Dual energy X-ray absorptiometry (DXA) scanning at baseline and week 9. For an overview of investigations and their timing see table 1.

**Table 1 T1:** Overview of investigations

	Interventions/Assessment domains	Tests/Evaluations	Screening	Baseline & treatment start	Active treatment phase	Treatment-free follow-up period
			
				Week 1	(Week 2-8)	(Week 9-14)
**Treatment**	Investigational drug	EPO (40,000 IU)/Placebo	-	1×	7× (weekly)	-

**Efficacy**	Neurocognitive functions	Neuropsychological testing (120 min)	-	1×	-	2× (week 9,14)
		
		MRI, fMRI and cognitive tests	1×	-	-	1× (week 14)
	
	Psychopathology	Clinical Rating	-	1×	1× (week 5)	2× (week 9,14)
		
		Questionnaires	-	1×	1× (week 5)	2× (week 9,14)
	
	Quality of life questionnaires		-	1×	1× (week 5)	2× (week 9,14)
	
	DXA scan		-	1×	-	1× (week 9)

**Safety**	Physical exam		1×	1×	7× (weekly)	3× (week 9,10,14)
	
	Vital signs		1×	1×	7× (weekly)	3× (week 9,10,14)
	
	Urine pregnancy test		1×	1×	3× (week 3,5,7)	-
	
	ECG		1×	-	2× (week 3,5)	-
	
	Adverse event monitoring		-	* Continuously until week 10*		
	
	Blood analysis	Haematology	1×	1×	7× (weekly)	3× (week 9,10,14)
		
		Blood chemistry	1×	1×	7× (weekly)	3× (week 9,10,14)
		
		BDNF, inflammatory and metabolic markers	-	1×	1× (week 5)	2× (week 9,14)

### Participants and screening

Patients with treatment-resistant major depression (study 1) and patients with bipolar disorder in full or partial remission but with cognitive problems (study 2) will be recruited through Clinic for Affective Disorders, Department of Psychiatry, Copenhagen University Hospital, Rigshospitalet. The centre receives patients with treatment-resistant major depression or bipolar disorder from the whole Capital Region. Patients will be screened with Schedules for Clinical Assessment in Neuropsychiatry (SCAN) [44] to confirm diagnosis.

Inclusion Criteria are a diagnosis of either treatment-resistant major depression (defined as failure to respond to at least two different types of antidepressants given in sufficient doses over sufficient time) in moderate to severe degree (HDRS score ≥ 17), or bipolar disorder in full or partial remission (HDRS ≤ 14 and YMRS ≤ 14) and subjective experience of moderate to severe cognitive problems on the CPFQ (score ≥ 4 on ≥ 2 domains), age between 18-65 years and unchanged antidepressant or mood stabilising treatment for minimum 2 weeks prior to inclusion in the study.

Exclusion criteria are any significant medical conditions (incl. diabetes, renal failure, epilepsy, untreated hypertension, present or past malignancies and thrombosis), smoking, hypertension, overweight (BMI > 30) or a body weight < 45 or > 95 kg, schizophrenia, present alcohol or substance misuse, acute suicidal risk, present or previous suicide attempts in the past 2 years, pregnancy or breast feeding, contraceptive medication, or a first-degree family history of thromboembolic events or seizure disorders.

A pregnancy test will be performed on female patients in their fertile age before and every second week during the study. Blood screening and physical examinations will be performed at baseline and every week during the treatment period as well as 1, 2 and 6 weeks after treatment cessation to monitor patients' level of red blood cells and ensure patient safety. Written informed consent will be obtained from all patients before their inclusion in the study and letters sent to their general practitioners to avoid any potential medical complications.

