#### Safety parameters and monitoring

Patient safety is monitored with medical examinations, blood pressure measurements, blood tests, ECG and other safety measures at baseline and throughout the study until 2 weeks after cessation of Epo/placebo treatment. For an overview of the safety tests, their frequency and timing see table 1.

If blood tests show significantly increased haematocrit (>50% for men and >48% for women) at two consecutive measurements within a week, bloodletting(s) (450 ml each) will be performed weakly with no cessation of treatment until haematocrit values are normalised. In the case of significant increase in thrombocytes (> 400 billion/L) or drop in reticulocytes (< 1‰) 2 repeated controls will be performed in the following week. If these values remain abnormal, the patient is taken out of the study and monitored with weekly medical examinations and blood tests until the values are normalised or is hospitalised for observation.

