There are also some risks and inconveniences for patients in the study. Although they will maintain their current antidepressant or mood stabilising treatment, they are requested to not make any changes in their medication for the duration of the study. This may give rise to ethical considerations for the acutely depressed patients in study 1. Nevertheless, these patients are characterised by treatment-resistance to currently available antidepressant medication and it is unclear which treatment would help this group. Therefore, keeping patients' treatment constant for the duration of the Epo/placebo treatment does not impose any significant ethical dilemmas. Finally, there are some health risks associated with Epo treatment as previously described. However, we consider these to be negligible in light of safety data from previous Epo studies and the described exclusion criteria, safety precautions and close safety monitoring performed throughout the study.

Given the above ethical considerations, we believe that participants' risks and inconveniences are minimal and outweighed by their benefits and by the potential implications of the trial for future management of mood symptoms and cognitive functioning in these patient groups.

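### No pregnancy test is scheduled after the last infusion (week 8); one urine test at the existing week-9 visit would close this cheaply, and the wording on test frequency should be made unambiguous

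*Protocol article*

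**What the plan says.** Participants and screening gives the rule for women of fertile age: "A pregnancy test will be performed on female patients in their fertile age before and every second week during the study". The next sentence sets out blood screening and physical examinations in different terms: "every week during the treatment period as well as 1, 2 and 6 weeks after treatment cessation". The exclusion criteria in the same section include "pregnancy or breast feeding, contraceptive medication".

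Table 1 (Study design) gives the schedule:

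- **Infusions:** one at week 1 and seven weekly in weeks 2 to 8.
- **Urine pregnancy test:** once at screening, once at week 1, then at weeks 3, 5 and 7. The cell for the treatment-free follow-up (weeks 9 to 14) holds a dash.
- **Physical examination, vital signs and blood tests:** also at weeks 9, 10 and 14.
- **Adverse event monitoring:** until week 10.

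Study design places "Dual energy X-ray absorptiometry (DXA) scanning at baseline and week 9". Safety parameters and monitoring does not mention pregnancy testing and defers to the table: "For an overview of the safety tests, their frequency and timing see table 1".

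**The concern.** The pregnancy-test row ends one week before dosing ends. The trial excludes pregnant women and also women on contraceptive medication, and this row is the only scheduled pregnancy check that the article gives. A pregnancy that began during the later dosing weeks could therefore go unnoticed by the trial, even though these women return at weeks 9, 10 and 14 for examination and blood tests.

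The wording adds a second, smaller problem. The sentence on pregnancy tests refers to the study, the next sentence refers to the treatment period, and the table stops within treatment. Site staff could reasonably ask which is meant.

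What is at stake is participant safety: recognising a pregnancy exposed to the study drug so that it can be followed up, and having a same-visit result before an X-ray procedure. Neither primary outcome is involved.

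**Working it through.** **Inputs** (Table 1 and Participants and screening): infusions at weeks 1 to 8, so 1 + 7 = 8, the last at week 8. Pregnancy tests from treatment start at weeks 1, 3, 5 and 7, so 4. Second DXA scan at week 9. Planned total 40 + 40 = 80 patients.

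**Step 1: does the table meet the fortnightly rule?** Count every second week from week 1 to each possible end of the study.

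| End point assumed | Tests due | Number due | Scheduled | Absent |
|---|---|---|---|---|
| Week 8 (last infusion) | 1, 3, 5, 7 | 4 | 4 | 0 |
| Week 10 (end of adverse event monitoring) | 1, 3, 5, 7, 9 | 5 | 4 | 1 (week 9) |
| Week 14 (end of follow-up) | 1, 3, 5, 7, 9, 11, 13 | 7 | 4 | 3 (weeks 9, 11, 13) |

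The table reproduces the rule exactly if it covers the treatment phase, and falls short only if it runs further.

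**Step 2: which end point is meant?** For the longer reading: the neighbouring sentence names the treatment period separately and uses it precisely. With the last infusion in week 8, its 1, 2 and 6 weeks after cessation give weeks 9, 10 and 14, which are the table's entries for examinations and blood tests. For the shorter reading: Ethical considerations describes one medication freeze in two ways, first saying of patients that "they are requested to not make any changes in their medication for the duration of the study" and then speaking of treatment kept constant "for the duration of the Epo/placebo treatment". The authors therefore do use the two words interchangeably in places. The article does not settle the matter.

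**Step 3: what holds on both readings?**

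- Last test to last infusion: 8 − 7 = 1 week, with no scheduled test afterwards.
- Infusions with no later scheduled test: 1 of 8 (week 8), or 2 of 8 (weeks 7 and 8) if the week-7 test is done before that week's infusion. The order is not stated.
- Last test to second DXA scan: 9 − 7 = 2 weeks, which is the promised interval.

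**Step 4: effect of one test at week 9.** In calendar order, every infusion would then have a later test, and the gap before the DXA scan would fall from 2 weeks to 0. This counts dates, not detection: a urine test one week after the last infusion may not show a conception close to that infusion.

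**The case against.** The strongest case on the other side is that nothing here is an error. Table 1 is explicit, with a dash under weeks 9 to 14, and the safety section sends the reader there for timing. Applied to the treatment phase, the sentence and the table agree. Nothing in the article promises a test after the last infusion, and the week-8 infusion breaks no fortnightly rule, since the next test would fall in week 9. No same-visit result before DXA is required either. An article condenses a fuller protocol, which may cover pregnancy follow-up, and patients remain under examination to week 14. The trial is also already running, so a new test is an amendment and not just an edit.

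Most of this stands. A reader might infer that the article contradicts itself and omits three promised tests. The documents do not support that as a flat statement, because it depends on a reading that the article leaves open. A reader might also infer that the DXA scan breaches the schedule, but the week-7 test lies within the stated interval. Nor would a week-9 test guarantee that every exposed pregnancy is found.

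What the objection does not remove is the gap itself. The article states a complete row for this test, not a summary, and that row ends before dosing does, in a trial that excludes users of contraceptive medication. The remedy uses a test already in use, at a visit already held.

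**Conclusion.** The point holds as a minor, low-cost improvement for participant safety. On either reading of the text, no scheduled pregnancy test follows the week-8 infusion, so 1 of 8 infusions (2 of 8 if testing precedes dosing at week 7) has no later check. The mismatch between text and table is conditional: 0 tests absent if the rule covers treatment, 1 if it runs to week 10, 3 if it runs to week 14.

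This rests on Table 1 being the full schedule of pregnancy tests; the complete protocol is not shown and could add one. The number of women of fertile age is not stated, so the number of participants affected cannot be given. The benefit is limited to recognising a pregnancy for follow-up, since a late test cannot undo exposure. Power, analyses and conclusions of both studies are unaffected.

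**What to change.** In Table 1, change the follow-up cell of the urine pregnancy test row from a dash to `1× (week 9)`, with the test done before the DXA scan. In Participants and screening, give the timing as *before, every second week during treatment and at week 9*. This closes the end-of-dosing gap and removes the ambiguity. A further test at week 10 or 14 would be optional; the article does not clearly call for one.

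The cost is one urine test per woman of fertile age at an existing visit: at most 1 × 80 = 80 tests, if every patient were such a woman. Because enrolment began in September 2009 and 21 patients had been randomised by October 2010, the change is a small amendment to a running, approved trial. Made at that date, it would reach the 80 − 21 = 59 patients still to be randomised and any randomised patient who had not yet passed week 9.

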### Randomisation

Block randomisation for the two studies has been performed by Pharma Consulting Group AB http://www.pharmaconsultinggroup.com. Pharma Consulting Group has created randomisation lists for each study and emergency envelopes for each patient ID number. Treatment groups are stratified for age (< or ≥ 35 years) and gender. Upon inclusion of participants, the date of birth, gender, diagnosis, and to which of the above strata the participant belongs are recorded. Numbering within each stratum is consecutive and study identification numbers are recorded in the patients' individual case report forms (CRFs).

### Blinding

Study personnel involved in the evaluation of outcomes and Epo/placebo infusions and study participants are blinded to study medication allocation. Blinding is maintained throughout the study, data management, outcome assessment and data analysis. This is possible because Epo is a clear colorless liquid similar to saline and because safety monitoring and bloodlettings are performed by a medic who is not involved in the evaluation of outcome measures or drug administration.

### Outcome assessments

The primary outcome for treatment-resistant depressed patients (study 1) is depression severity as measured with the HDRS-17 [1] at week 9. Global Assessment of Function (GAF) scores at week 9 will be reported in addition to the primary outcome. The secondary outcome is remission defined as HDRS score ≤ 8 at week 9. Confidence intervals will be reported in relation to the proportions in remission. The tertiary outcomes are memory and executive functions, measured with the Rey Auditory Verbal Learning Test (RAVLT) [2,3] and Rapid Visual Processing (RVIP) test from the Cambridge Neuropsychological Test Automated Battery (CANTAB), respectively, facial expression recognition measured with a facial expression recognition test, as well as self-ratings of cognitive difficulties on the CPFQ, depressive symptoms and life quality at week 9.

For bipolar patients in remission (study 2) the primary outcome is memory performance measured with the RAVLT at week 9. The secondary outcome is sustained attention measured with the RVIP test and recognition of emotional facial expressions assessed with a facial expression recognition test at week 9. Finally, the tertiary outcomes are ratings of mood, symptoms, quality of life and cognitive function at week 9.

Clinical mood ratings and patients' self-ratings will be performed at baseline, and weeks 5, 9 and 14 to assess the speed and duration of potential effects on these measures. Neuropsychological testing is performed at baseline, and weeks 9 and 14 to assess effects of Epo vs. placebo treatment and their duration. For overview see table 1.

